### Randomization and blinding

Allocation of participants to either condition will be established using a computer generated block randomization procedure (block size n = 4) without stratification. The written information to inform patients about the study only mentions that two types of GMT will be compared. To achieve participant blinding, no information will be given about specific differences between the two conditions. Assessor blinding will be achieved by filming the (i)ADL task performance of the participants. All hints of treatment condition will be avoided and performance will be scored by research assistants who are not involved in delivering GMT.

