**Methods/Design:**

The study is a double blind randomized controlled trial, in which the efficacy of Goal Management Training with an errorless learning approach will be compared with conventional Goal Management Training, based on trial and error learning. In both conditions 32 patients with acquired brain injury of mixed etiology will be examined. Main outcome measure will be the performance on two individually chosen everyday-tasks before and after treatment, using a standardized observation scale and goal attainment scaling.

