#### Setting

Patients will be recruited from the Rehabilitation Medical Centre Groot Klimmendaal in Arnhem, the Netherlands and the outpatient rehabilitation clinic for brain injured patients and the department of Neurorehabilitation of the Sint Maartenskliniek in Nijmegen, the Netherlands. In the course of 18 months 64 participants will be recruited.

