**Figure 2 F2:**
[figure not shown]
Flowchart of the study design.

After fulfilling the inclusion criteria and obtaining the signed informed consents, participants will be randomly assigned to GMT with an errorless learning approach (experimental treatment) or to conventional GMT (treatment as usual) using trial and error learning.

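### One published block size of 4, with trainers who know the arm, makes allocation partly predictable, and chance imbalance between centres is neither stratified nor adjusted for

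*Protocol article*

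**What the plan says.** Randomization and blinding sets allocation "using a computer generated block randomization procedure (block size" 4), without stratification. Setting names a rehabilitation centre in Arnhem and, in Nijmegen, "the outpatient rehabilitation clinic for brain injured patients and the department of Neurorehabilitation" of a second institution. That makes two institutions, or three recruiting units if the two Nijmegen units count separately. The same section gives the target: "In the course of 18 months 64 participants will be recruited". The Abstract gives the arm size: "In both conditions 32 patients with acquired brain injury of mixed etiology will be examined".

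On timing, the Procedure section states: "After fulfilling the inclusion criteria and obtaining the signed informed consents, participants will be randomly assigned". Interventions then places the choice of goals in session 2 and the baseline film after it.

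The two condition descriptions require opposite behaviour from the therapist: active prevention of errors in one arm, no prompting in the other. Trainers therefore cannot be blind, and the blinding covers participants and film raters only.

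Statistical analysis sets out a 2 × 2 repeated-measures model with treatment condition and measurement as its factors. Its ANCOVA fallback concerns age, education and estimated IQ, and applies only if these differ significantly. Centre is not named.

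**The concern.** Two separate weaknesses follow from these choices.

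- **Predictability.** With a known fixed block of 4, a person who follows past allocations can work out how each block must end. If that person influences who is enrolled and when, allocation can affect selection. Blind scoring of films cannot undo this, because it protects the rating and not the make-up of the groups.
- **Centre.** An unstratified list holds the arms equal overall, not within each centre. This is a therapist-delivered treatment, and therapists plausibly differ by centre (the article does not say). If the arms draw unequally on the centres, part of any centre difference in improvement is counted as treatment effect, and the stated model has nothing to remove it.

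**Working it through.** **Inputs.** From the article: block size 4, two arms, 64 patients, 32 per arm, no stratification, two institutions. Assumed, because the article does not give them: the split of patients between centres, patients arriving from the centres in random order, and the size of any centre difference.

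**1. The plan's own figures.** 64 / 4 = 16 complete blocks, each with 2 patients per arm, so 16 × 2 = 32 per arm. This agrees with the article.

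**2. Predictability for someone who sees all past allocations.** Take the four positions in a block in turn.
- Position 1: nothing is known, so the best guess is right with probability 1/2.
- Position 2: three places remain, two of them in the other arm, so 2/3.
- Position 3: with probability 1/3 the first two were alike and the third is certain. Otherwise (2/3) it is even. Together 1/3 × 1 + 2/3 × 1/2 = 2/3.
- Position 4: always certain, so 1.

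Share known for certain: (1/3 + 1) / 4 = 33.3%, or about 21 of 64.

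Best-guess rate: (1/2 + 2/3 + 2/3 + 1) / 4 = 70.8%, or about 45 of 64, against 32 by chance.

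**3. Predictability for someone who sees one centre only.** This was simulated with 40,000 shared lists of 64. The rule was to guess the arm currently behind at one's own centre. It was right 54% of the time with a 50/50 split, and 53% for a centre with 30% of patients. Long runs of patients from a single centre would raise this.

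**4. Within-centre imbalance on the shared list.** Let D be the arm difference in one centre, and let each patient come from that centre with probability p. The arms are equal overall, so Var(D) = 64 × p(1 − p).
- p = 0.5: variance 64 × 0.25 = 16, SD 4, mean absolute difference about 0.8 × 4 = 3.2.
- The simulation agrees (3.2 in a centre of about 32): 2 or fewer in 47% of trials, 4 or more in 38%, 6 or more in 17%, 8 or more in 6%.
- p = 0.3 (a centre of about 19): mean 2.9, and 6 or more in 13%.
- Three equal sites: the worst site differs by 6 or more in 31%.

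**5. What that does to the estimate.** With 32 per arm, the arms' shares from one centre differ by D/32. If the centres differ by δ in mean change, the treatment contrast shifts by (D/32) × δ.
- D = 3.2 means about 55% against 45%. With an assumed δ of 0.5 SD the shift is 0.10 × 0.5 = 0.05 SD.
- D = 8 gives 0.25 × 0.5 = 0.125 SD.
- With δ = 0.25 SD both figures halve.

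For scale, the design effect is d = 0.6. A centre difference that is the same before and after treatment cancels in the treatment-by-time contrast, so only differences in change count.

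**6. What varying the block size would gain.** In simulated lists of 32, someone who saw the whole list guessed 68.9% right with sizes 4 and 6, and 67.5% with sizes 4, 6 and 8. Against 70.8%, that is a gain of 2 to 3 points. Separate centre lists of this kind would expose those same rates to local staff, who on the shared list reach about 54%.

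**The case against.** The strongest reply is that the two harms pull against each other. The 71% needs sight of the whole sequence across both cities. On the single shared list that permits centre imbalance, staff at one centre are close to guessing. This stands, and it is why the two rates must be given together.

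Selection also requires that those who enrol know past allocations. The article does not say who enrols or who holds the list, and an article commonly leaves that to the full protocol. Eligibility rests largely on test cut-offs, which narrows discretion, although some exclusions call for judgement. This stands too: the route is possible, not shown.

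A reader might infer that a predictable block lets trainers steer the choice of goals. The documents do not support that. Participants choose their goals, with GAS levels completed jointly with the trainer. Assignment is described before the sessions begin, so a trainer may already know the arm at session 2. Any influence there would come from the timing of assignment, whatever the block size.

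Leaving centre unstratified with two institutions and 64 patients is a common choice, and an analysis plan not shown here might add a centre term. That tempers the point but does not remove it: the article does state its primary model and its adjustment rule, and centre is in neither.

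**Conclusion.** The point holds in a limited form. A fixed, published block of 4 combined with trainers who know the arm is avoidably predictable: one third certain and 71% guessable with full sight of the list, about 54% from one centre. Separately, the unstratified list and a model without centre leave chance imbalance of about 3 patients in a centre of 32 unadjusted.

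That the arms will be unbalanced within each centre should not be inferred. It is a chance risk, with a difference of 2 or fewer in nearly half of trials. Its direction is random, and the typical shift is about 0.05 SD.

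The centre figures rest on an assumed even split, random arrival order and an assumed 0.5 SD centre difference in change. The 33.3% and 70.8% follow from the block size alone, given full sight of earlier allocations. The case for acting is that the remedy is cheap, not that the threat is large.

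**What to change.** - **Analysis.** Pre-specify centre as a between-subject factor in the primary repeated-measures model, including its interaction with measurement, since only centre differences in change affect the treatment contrast. Cost: one degree of freedom for two centres or two for three sites, taking the error term from 64 − 2 = 62 to 61 or 60. This can be done even if recruitment has closed, provided it is fixed before analysis.
- **Allocation, for patients still to be randomised.** Use randomly varying, undisclosed block sizes on a list held by someone who neither treats nor enrols. Most of the benefit comes from keeping the list and past allocations away from enrolling staff, because varying the block size lowers the guess rate by only 2 to 3 points. Cost: a new computer-generated list, an amendment line, and a small possible imbalance if the list stops inside a block (at most 2 patients in the simulated lists of 32 with sizes 4 and 6, up to 4 with sizes 4, 6 and 8).
- **Optional.** Separate lists per centre improve balance within centre but raise what local staff could guess from about 54% to about 68%. Use them only with strict concealment.

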### Statistical analysis

All data will be analyzed with IBM SPSS 19. The normality of all variables will be checked and corrected for, if necessary. The performance on the neuropsychological tests will be compared with normative data and corrected for age and education. Descriptive statistics of relevant variables will be obtained and compared for the two treatment arms using analysis of variance.

To evaluate the efficacy of GMT-errorless learning compared to conventional GMT with trial and error learning, pre- and post training data will be analyzed using a 2 × 2 repeated measure analysis of variance (General Linear Model) with treatment condition (GMT-errorless learning and conventional GMT) as between-subject factor and measurement (pre- and post-treatment) as within-subject factor. The dependent variable will be the standardized scale score (quantitative). The same analysis will be done for the secondary outcome measure, the GAS scores. Appropriate post-hoc tests will be performed and effect sizes (partial eta-squared) will be computed. Moreover, correlations will be computed between moderator variables (questionnaires and neuropsychological tests) and treatment effects (difference score: post treatment minus baseline).

The background variables of the participants in both treatment conditions are expected to be comparable (age, education level, estimation IQ) because of the randomization procedure. In case of significant differences, appropriate statistical adjustment for confounding variables will be performed (ANCOVA). All statistical tests will be two-tailed, alpha set at 0.05.

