### Sample size

Determination of the sample size for this study is based on data from a RCT examining the effects of a structured 6-week Goal Management Training
[17]. In each group 32 participants are required to detect an effect size of *d =* .6 with a power = .80 and α. = 05. These estimated sample sizes are comparable with other studies evaluating the efficacy of different types of GMT
[17,54].

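### The planned repeated-measures ANOVA is a valid change-score test, but ANCOVA on the baseline task score would be more precise at almost no cost

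*Protocol article*

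**What the plan says.** Under Statistical analysis, the protocol article states that "pre- and post training data will be analyzed using a 2 × 2 repeated measure analysis of variance (General Linear Model"), crossing treatment condition with time of measurement and taking the standardized task-scale score as dependent variable. It does not say which term tests efficacy. In this design, that is the condition-by-time interaction. The same section defines treatment effects for the moderator correlations as post minus baseline. It adds: "Appropriate post-hoc tests will be performed and effect sizes (partial eta-squared) will be computed".

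ANCOVA appears only conditionally, as an adjustment for background variables (age, education and estimated IQ are the examples) that turn out to differ significantly between arms. The baseline task score is not named as a covariate. It is nevertheless collected: under Interventions and Baseline, task performance is filmed and scored after session 2, before the arms diverge in sessions 3 to 8.

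For sample size the article says "In each group 32 participants are required to detect an effect size of" d = 0.6 "with a power = .80". The statistical section adds "All statistical tests will be two-tailed, alpha set at 0.05". Neither place gives a pre-post correlation or says whether d is scaled by the SD of the post-treatment score or by the SD of the change.

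**The concern.** A change score subtracts the whole baseline value, which amounts to assuming that baseline predicts outcome with a slope of exactly 1. If the true slope is lower, subtraction over-corrects and adds noise. ANCOVA estimates the slope and removes only what baseline actually predicts.

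Two things are at stake in a trial of 64 patients. One is power. The other is how a chance baseline difference on self-chosen tasks feeds into the estimated effect, given that allocation uses a "computer generated block randomization procedure (block size n = 4) without stratification". The second is the individual-trial face of the same imprecision and should not be counted as a separate harm.

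**Working it through.** **Inputs.** From the article: 32 per arm, d = 0.6, power 0.80 (Sample size); two-sided alpha 0.05 (Statistical analysis); one pre and one post measurement. Assumed, because the article does not give them: pre-post correlation r from 0.3 to 0.9, and equal pre and post SDs unless stated otherwise.

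**Step 1: the plan's own figure.** For a plain two-group comparison, n per arm = 2(1.960 + 0.842)² / 0.6² = 43.6, so 44 by the normal approximation and 45 with the t distribution. A one-sided test would need 35 or 36. The stated 32 is not reproduced. At 32 per arm, the plain comparison has 66% power (t). This is a sample-size matter in its own right. Here it only serves as the reference point.

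**Step 2: what the ANOVA tests.** With two time points, the interaction F is the square of the t statistic for the arm difference in post minus pre.

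**Step 3: variances.** Let s0 and s1 be the pre and post SDs.
- Change score: s0² + s1² − 2r·s0·s1
- ANCOVA: s1²(1 − r²)
- Difference: (s0 − r·s1)², which is never negative

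With s0 = s1, relative to the post-score variance, these are 2(1 − r) and 1 − r². Their ratio is 2/(1 + r): 2/1.3 = 1.54, 2/1.5 = 1.33 and 2/1.7 = 1.18 at r = 0.3, 0.5 and 0.7.

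**Step 4: power if d = 0.6 is in post-score SDs.** Effective d is 0.6/√(2(1 − r)) for change and 0.6/√(1 − r²) for ANCOVA. The noncentrality is effective d × √(32/2) = 4 × effective d, with 62 and 61 degrees of freedom.

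| r | effective d, change | power | effective d, ANCOVA | power |
|---|---|---|---|---|
| 0.3 | 0.507 | 51% | 0.629 | 70% |
| 0.5 | 0.600 | 66% | 0.693 | 78% |
| 0.7 | 0.775 | 86% | 0.840 | 91% |

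The planned test reaches 80% at r of about 0.64, and ANCOVA at about 0.54. A simulation of 4,000 trials at r = 0.5 gave 65% for the interaction and 77% for ANCOVA, in line with the formulas.

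**Step 5: power if d = 0.6 is in change-score SDs.** The planned test then has effective d = 0.6 and 66% power whatever r is. ANCOVA has effective d = 0.6 × √(2/(1 + r)).

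| r | change | ANCOVA |
|---|---|---|
| 0.3 | 66% | 83% |
| 0.5 | 66% | 78% |
| 0.7 | 66% | 73% |
| 0.9 | 66% | 68% |

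On this scale ANCOVA reaches 80% only for r up to about 0.42.

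**Step 6: unequal SDs.** At r = 0.5, with d in post-score SDs, change versus ANCOVA is 50% vs 78% if the post SD is 0.75 times the pre SD, and 76% vs 78% if it is 1.5 times. The gap can therefore be wider or narrower than in Step 4.

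**Step 7: chance imbalance.** The standard error of the baseline difference between arms is √(2/32) = 0.25 SD. Given a difference of that size, the change-score estimate shifts by (1 − r) × 0.25 SD, which at r = 0.5 is 0.125 SD, or 0.125/0.6 = 21% of the planned effect. ANCOVA removes this shift.

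**Step 8: cost of estimating the slope.** With 64 patients the ANCOVA variance is inflated by about 1 + 1/60 = 1.017. Multiplied by (1 + r)/2, the ANCOVA-to-change ratio is 0.966 at r = 0.90, 1.001 at 0.97 and 1.012 at 0.99.

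**The case against.** The strongest reply is that nothing here is an error. Under randomisation the interaction test is unbiased and keeps its 5% level, and the article does not contradict itself on this point. That stands: this is a matter of efficiency, not validity. Several stronger readings are tempting, and the document does not support them.

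- *The baseline is wasted.* It is not. A change score uses it, with the slope fixed at 1.
- *ANCOVA is never less precise.* That is a large-sample statement. With 64 patients it fails above r of about 0.97, by about 1%.
- *ANCOVA restores the missing power.* This depends on r and on the SD scale of d, and the article gives neither. On the post-score scale no power is missing above r of about 0.64, while at r = 0.3 ANCOVA still leaves 70%. On the change-score scale the gain falls from about 18 points at r = 0.3 to 2 at r = 0.9.
- *Choosing tasks one does badly biases the comparison through regression to the mean.* Goals are chosen in session 2 and baseline follows, all before the arms differ, so the expected effect is the same in both arms and cancels.
- *The post-hoc tests are within-arm comparisons offered as evidence of efficacy.* The article calls them only appropriate post-hoc tests, and it frames efficacy as one condition against the other.

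The 32-versus-45 gap also belongs to the sample-size section and should not be used to enlarge this point. With all of that granted, the variance inequality in Step 3 remains, and the plan reserves ANCOVA for background variables.

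**Conclusion.** The point holds as an efficiency improvement. The planned primary test is valid but less precise than a baseline-adjusted ANCOVA over any plausible correlation. With equal SDs its variance is 1.54 to 1.18 times as large for r between 0.3 and 0.7. In power terms, across the cases tabulated, the gain runs from about 18 points (r = 0.3, either scale) down to 2 (r = 0.9, change-score scale). ANCOVA can recover part of any shortfall, and how much cannot be settled from the document. The algebra is certain. The power figures rest on the assumed r, on equal SDs and on which SD scales d. The equal-SD assumption is open to doubt for a bounded percentage score on tasks the patient finds difficult. The change is worth making because it is nearly free, not because the present analysis would mislead.

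**What to change.** Replace the primary-analysis sentence so that the treatment effect is estimated by ANCOVA: post-treatment percentage score as outcome, treatment arm as factor, baseline percentage score as covariate in every case and not conditional on a significance test. Report the adjusted mean difference with its 95% CI. Keep the 2 × 2 repeated-measures ANOVA as a sensitivity analysis. When the sample-size paragraph is next revised, state the assumed pre-post correlation and the SD to which d = 0.6 refers.

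The data and the SPSS General Linear Model procedure stay the same. The cost is one degree of freedom, with a loss of precision of about 1% only if r is very close to 1. How the two task scores per participant are combined is a separate decision, which this change neither requires nor settles.

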## Methods/Design

To evaluate the efficacy of GMT in which errorless learning is integrated, this approach will be compared with conventional GMT treatment in which an errorful approach is used. This comparison will be investigated in a double blind randomized controlled trial that is registered at the Dutch Trial Register (No. NTR3567). The Medical Review Ethics Committee region Arnhem-Nijmegen approved the study (No. NL38019.091.11).

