### Post-treatment

After treatment, (i)ADL task performance will be assessed again by filming and scoring task performance. The previous completed GAS schemes will be scored by participant and by trainer to evaluate goal attainment. The questionnaires and neuropsychological assessment, using parallel versions of the same tests, will be administered after treatment as well, to control for nonspecific recovery. The data gathered with the questionnaires and the neuropsychological tests provide measures for change in insight, executive complaints, subjective and objective executive functioning for moderator analyses, to examine possible determinants for treatment success.

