## Discussion

Both Goal Management Training and errorless learning are two methods that have been separately well studied and shown to be effective. Up to now however, the two methods have never been combined. Combining an errorless learning approach with GMT is expected to optimize the acquisition of the GMT algorithm and improve the performance of complex daily tasks in brain-injured patients with executive deficits. Consequently, the efficacy of the intervention is increased, which may contribute to functional independence of patients with acquired brain injury. Not only does the combination of methods provide an evidence-based intervention for clinical practice, the present study may also contribute to more insight into the underlying mechanisms of errorless learning. Previous studies investigating errorless learning have often focussed on patients with profound memory impairments, such as patients with Alzheimer’s disease or Korsakoff’s syndrome
[26,30]. The assumption was that due to a dysfunctional explicit memory system errors were not consciously corrected and implicitly consolidated
[31]. However, the beneficial effects of errorless learning may also be related to a failing error monitoring system. That is, the inability of patients with executive dysfunction to detect errors
[38]. The current study proposal focuses on patients with primarily executive impairments in whom the presence of memory impairments is less prominent. This suggests that explicit memory is relatively spared in these patients, whereas their error-monitoring system is failing. As a result, the current study may contribute to a better understanding of these two underlying mechanisms of errorless learning.

Previous studies evaluated GMT used paper-and-pencil tasks
[7] or fixed (i)ADL tasks, such as meal preparation
[7] and financial management
[15]. A strength of this study is that participants will choose their own individual (i)ADL tasks that will be (re)learned during the training. Individual goals correspond to individual lifestyles and demands and may therefore provide a more fitting contribution to daily functioning and enhance functional independence of the participants.

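### The planned moderator analysis correlates tests and questionnaires with pre-post change, which identifies who improves and not who gains more from errorless than from conventional GMT

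*Protocol article*

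**What the plan says.** The Statistical analysis section of the protocol article first sets out a repeated-measures analysis of variance "with treatment condition (GMT-errorless learning and conventional GMT) as between-subject factor and measurement (pre- and post-treatment) as within-subject factor". No other variable enters that model. It then adds that "correlations will be computed between moderator variables (questionnaires and neuropsychological tests) and treatment effects (difference score: post treatment minus baseline"). So the treatment effect in this step is each participant's own change, and the variables correlated with it are called moderators. The sentence gives no time point for those variables and does not say whether the correlations are pooled or run per arm.

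The Post-treatment section fills in part of this. The questionnaires and neuropsychological tests "will be administered after treatment as well, to control for nonspecific recovery". The data "provide measures for change in insight, executive complaints, subjective and objective executive functioning for moderator analyses", and the aim is "to examine possible determinants for treatment success".

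On the comparator, the opening of Methods/Design says of GMT with errorless learning that "this approach will be compared with conventional GMT treatment in which an errorful approach is used". Table 2 shows the tests measured at recruitment and the questionnaires at baseline, and both again after treatment.

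**The concern.** Two things are wrong with the rule as stated.

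First, the quantity. Both arms receive active GMT, so post minus baseline contains the response common to both arms, nonspecific recovery (which the article itself mentions), retest effects and regression to the mean, together with any effect of errorless learning. A variable that correlates with this sum may be only a marker of who improves under either form of GMT. A moderator of the errorless-learning effect is a variable on which the difference between arms depends.

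Second, the timing. A change score on a test or questionnaire needs the post-treatment assessment. It is measured after randomization and treatment can alter it. It may be a mediator or a concurrent outcome, but it cannot be a moderator.

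At stake is the interpretation of a secondary analysis: prognostic variables, or variables that merely improve alongside the outcome, could be reported as moderators of the treatment.

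**Working it through.** **Inputs.** From the article: 32 participants per arm (Sample size: "In each group 32 participants are required to detect an effect size of" d = 0.6) and a two-sided alpha of 0.05 (Statistical analysis). The article gives no figure for the moderator analysis, so there is none to reproduce. Assumed: a standardized moderator, a standardized change score and the slopes named below. The arm effect on change is set to 0.6 standard deviations, borrowing the size of the planning effect.

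**Step 1. What each method estimates.** Write change = a + 0.6 × arm + slope(arm) × moderator + error. Moderation of the errorless-learning effect is the difference between the two slopes. With equal arms, a pooled correlation reflects roughly the average of the two slopes. The average can be large when the difference is zero, and zero when the difference is large.

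**Step 2. A prognostic variable without moderation.** Take a correlation of 0.4 with change in both arms and a within-arm variance of 1.
- The arm effect adds 0.6² × 0.25 = 0.09 to the pooled variance, so the pooled correlation is 0.4 / √1.09 = 0.383.
- Fisher's z: atanh(0.383) × √(64 − 3) = 0.404 × 7.81 = 3.15.
- Chance of significance: Φ(3.15 − 1.96) = Φ(1.19) = 0.88.
- Simulation (5,000 trials): 0.889 for the correlation, 0.047 for the interaction test.

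**Step 3. The same variable, correlations run per arm.** Here n = 32, and atanh(0.4) × √29 = 0.424 × 5.39 = 2.28, so each arm is significant with probability Φ(2.28 − 1.96) = 0.63. Exactly one arm is significant in 2 × 0.63 × 0.37 = 0.47 of trials, although the slopes are equal. Per-arm correlations therefore do not solve the problem unless they are formally compared.

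**Step 4. Range over assumed slopes** (10,000 trials per row, residual standard deviation 1; share of trials significant):

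| Slopes (errorless, conventional) | Moderation | Pooled correlation | Interaction test |
|---|---|---|---|
| 0, 0 | none | 5% | 5% |
| 0.5, 0.5 | none | 95% | 5% |
| 0.5, 0 | yes | 44% | 47% |
| 0.3, −0.3 | yes, crossover | 6% | 62% |
| 0.5, −0.5 | yes, crossover | 7% | 96% |

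The second row carries the point: there is no moderation and the correlation is nearly always significant.

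**Step 5. Change used as the moderator.** Let a shared recovery factor drive both the change in a test and the change in the outcome, with loading 0.7 and independent error of standard deviation 0.7 in each, and let nothing modify the treatment effect. The expected correlation is 0.49 / √(0.98 × 1.07) = 0.48. In 5,000 trials it was significant in 98%, against 6% for an unrelated baseline measure.

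**Step 6. Power of the correct test.** For 80% power the two arms' correlations must differ on Fisher's scale by (1.96 + 0.84) × √(2/29) = 0.74. With one arm at zero, the other must be tanh(0.74), about 0.63.

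**The case against.** The best defence is that the stated aim is broad. Determinants of success can fairly include predictors of improvement, and correlations with change are a legitimate way to look for those. On this view much of the fault is the word moderator. That is right as far as it goes, and relabelling is one of the two acceptable repairs. It does not rescue the analysis as named, because the article calls the variables moderators and calls individual change the treatment effect.

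It can also be said that pooling is not stated, that the sentence in Statistical analysis names no time point, and that every instrument has a pre-treatment value. All three hold. The pooled percentages are therefore conditional on pooling, although per-arm correlations without a comparison fail too. The objection to change as a moderator rests on the Post-treatment section alone. Nothing in the article rules out the use of pre-treatment values as well.

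A reader might infer four stronger points that the article does not support.
- That the Discussion makes a promise which this analysis cannot keep. It says "the current study may contribute to a better understanding of these two underlying mechanisms of errorless learning", but it derives this hedged statement from a sample whose deficits are mainly executive, with memory less affected. It does not invoke the moderator analysis.
- That real moderators would generally be missed. This holds mainly for crossover effects. With slopes 0.5 and 0 the two tests detect about equally often (44% and 47%).
- That multiplicity counts against correlations in particular. For the 15 instruments in Table 2, 1 − 0.95^15 = 0.54, but this assumes independence, seven of them measure executive functioning, and the same figure would apply to 15 interaction tests.
- That the efficacy result is compromised. The condition-by-time comparison contains no moderator and is untouched.

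**Conclusion.** The concern holds for the analysis as the article defines and labels it. Correlating tests and questionnaires with post-minus-baseline change finds correlates of improvement under GMT. It does not show for whom errorless learning adds more than conventional GMT. Change measured after treatment does not qualify as a moderator of that treatment.

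Under the assumptions above, a prognostic variable with no moderating role is significant in about 89% of trials by pooled correlation and about 5% by the interaction test. The percentages depend on the assumed slopes and on pooling. The mismatch between the correlation and moderation depends on neither. This is a stated definition that answers a different question, not a detail left to another document. It concerns a secondary analysis, deserves correction, and is cheap to correct.

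**What to change.** Replace the moderator sentence with an interaction model: post-treatment task score on arm, baseline task score, the recruitment or baseline value of the candidate moderator, and arm by moderator. Restrict it to a few moderators named in advance, for example the RBMT-III and one executive measure whose construction is written down. Report each interaction estimate with its 95% confidence interval and label the set exploratory. An executive measure built from the selection tests should not be presented as a measure of error monitoring without support, and selection on those tests will narrow its range.

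If the correlations with change are kept, describe them as predictors of improvement (pre-treatment values) or associates of improvement (changes in tests or questionnaires), and reword the Post-treatment section to match.

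The cost is wording and a small amount of analysis. Every variable is already collected. The downside is low power: at 32 per arm only a very strong interaction is likely to be detected, so wide intervals should be expected and a null result should not be read as absence of moderation.
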